#### Sample size and sampling

There will be three levels of sampling for this study. The first level is county sampling, where we will purposively sample four counties already implementing autonomy reforms, four planning to implement the intervention and four not implementing as control. From the sampled counties, we will randomly sample 80 health facilities per group, assuming a mean difference of 10% in facility readiness between the two groups and a population variance of 400 across the groups using 80% power, 95% confidence level and a design effect of 1.2. Because the autonomy reforms have the biggest effects on facilities that raise revenue, we will sample all facilities from levels 4–6 from the selected counties. Leve 4-6 facilities are allowed by law to charge user fees. For the remaining facilities, we will then randomly sample levels 2 and 3. The numbers will be proportionate, targeting a maximum 20 facilities per county. For clients, we will randomly sample a minimum of 1600 clients exiting the health facilities per group, assuming a mean difference of 10% in client satisfaction between the two groups and a population variance of 55 across the groups using 80% power, 95% confidence level and a design effect of 3. To calculate the variance, we took an average of the outcome of the interest in the control and intervention (expected).^28^,^30^ We divide the 1600 clients equally among the selected facilities to achieve a minimum sample of 20 per facility as is recommended for cluster randomised trials.^28 30^ The following sample size calculation formula was used:

,$$n=\left(Z_{\alpha /2}+Z_{\beta \;}\right)sqrd\times 2\times \;\sigma^{2}\;/d^{2}$$

where Z_α/2_=1.96 (5% significance), Z_β_=0.84 (80% power), σ^2^=population variance of 59 (SD of 19 per group) and d=mean difference of 8% between the two groups.

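### The 1600 clients per group do not follow from the stated inputs, which give 26, and the formula legend contradicts itself and matches neither calculation

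*Protocol article*

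**What the plan says.** All the relevant text is in the Protocol article, in the section on sample size and sampling under the evaluation of the effects of the reforms.

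- **Facilities:** 80 per group, for a 10% difference in readiness, variance 400, 80% power, 95% confidence and a design effect of 1.2.
- **Clients:** at least 1600 per group. The stated basis is "assuming a mean difference of 10% in client satisfaction between the two groups and a population variance of 55 across the groups". Power and confidence are the same as for facilities, but the design effect is now 3.
- **Source of the variance:** "To calculate the variance, we took an average of the outcome of the interest in the control and intervention (expected").
- **Allocation:** "We divide the 1600 clients equally among the selected facilities to achieve a minimum sample of 20 per facility".
- **Formula:** n = (Zα/2 + Zβ)² × 2 × σ² / d², presented as the one used, with "Z_α/2_=1.96 (5% significance), Z_β_=0.84 (80% power"). The other symbols are defined by "population variance of 59 (SD of 19 per group) and d=mean difference of 8% between the two groups".

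The primary study design section names facility readiness as the primary outcome. Client satisfaction is one of the other outcomes.

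**The concern.** The section gives three sets of inputs: one for facilities, one for clients, and a third in the legend that names no outcome. A variance of 55 with a difference of 10 means an SD of 7.4, so the target difference is larger than one SD. A comparison of that kind needs very few people, even after a design effect of 3, yet the plan asks for 1600. The legend raises a second doubt, because its variance and its SD cannot both be right and its difference of 8 appears nowhere else.

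At stake is the power statement for client satisfaction. As printed, a reader cannot say what difference 1600 clients were meant to detect, or with what variability. The eventual report would have no sound basis for saying that this comparison was adequately powered.

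**Working it through.** **Inputs.** Z values 1.96 and 0.84 come from the legend. The differences, variances and design effects (DE) are those listed above. The common factor is (1.96 + 0.84)² × 2 = 7.84 × 2 = 15.68.

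**1. Facilities, from the plan's own inputs.**
15.68 × 400/10² = 62.7; × 1.2 = 75.3. The stated 80 is consistent with this, rounded up to 4 counties × 20 facilities. Power at 80 per group: SE = √(2 × 400 × 1.2/80) = 3.46; 10/3.46 − 1.96 = 0.93; Φ(0.93) ≈ 82%. This calculation stands.

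**2. Clients, from the plan's own inputs.**
15.68 × 55/10² = 8.62; × 3 = 25.9, so 26 per group. The plan states 1600, and 1600/25.9 ≈ 62.

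**3. Variance needed to reach 1600.**
- At d = 10, DE 3: (1600/3) × 100/15.68 = 3401 (SD 58.3). The largest variance possible on a 0–100 scale is 50² = 2500, so no satisfaction measure in percent can supply it.
- At d = 8, DE 3: (1600/3) × 64/15.68 = 2177 (SD 46.7). This is possible, but it is none of 55, 59 or 361.

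**4. The legend.**
19² = 361, while √59 = 7.7, so the two figures disagree.

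| Legend reading, d = 8 | DE 1 | DE 1.2 | DE 3 |
|---|---|---|---|
| Variance 59 | 14.5 | 17.3 | 43.4 |
| SD 19 (variance 361) | 88.4 | 106.1 | 265.3 |

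No cell gives 80 or 1600.

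**5. Other routes to 1600.** Three calculations come close, and each changes at least one stated input:
- 59 read as an SD, with d = 10 and DE 3, gives 1637. That variance, 3481, is again above 2500.
- A binary variance of 55 × 45 = 2475, with 90% power, gives 1560.
- 55 read as an SD, with a one-sided test and 90% power, gives 1554.

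The simple product 80 × 20 gives exactly 1600.

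**6. What 1600 might deliver (illustration only).** Assume that satisfaction is binary with a mean near 55%, DE 3, and a comparison at one time point. The document states neither the binary scale nor the 55%.
- Variance 2475; SE = √(2 × 2475 × 3/1600) = 3.05 points.
- Number needed for 10 points: 15.68 × 2475/100 × 3 = 1164.
- Power at 10 points: 10/3.05 − 1.96 = 1.32, about 91%.
- Power at 8 points: 8/3.05 − 1.96 = 0.67, about 75%.
- Difference detectable with 80% power: 2.8 × 3.05 ≈ 8.5 points.

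If satisfaction is instead a score with SD 19, 170 per group would do at d = 10 and 265 at d = 8, both with DE 3.

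**The case against.** The strongest reply is that the primary outcome is unaffected. Facility readiness has its own inputs, stated beside it, and they support 80. The number of clients may have been set by the target of 20 per facility, since 80 × 20 = 1600. On plausible assumptions that number is ample for the stated 10 points. All of this stands, and it limits the point to a faulty justification. It does not rescue the text, which presents 1600 as the product of a 10% difference, a variance of 55 and a design effect of 3.

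Three stronger readings are tempting, and the document does not support them.

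- **An average satisfaction level was entered as the variance.** The averaging sentence suggests this, and 55 and 59 are the midpoints of pairs such as 50/60 and 55/63. Those pairs are not in the document, and the sentence may be loose wording for averaging two variances. The facility variance of 400 cannot be an average of percentages. Nor would the mistake explain 1600, because entering 55 gives 26.
- **The facility sample is underpowered.** With SD 19, d = 8 and DE 1.2, 106 facilities would be needed, and 80 would give about 68% power. But the legend names no outcome and no design effect, and its equally printed variance of 59 would need only about 17. A legend that contradicts itself cannot establish a shortfall.
- **The variance should be 0.55 × 0.45.** The plan speaks of a mean difference and never says that satisfaction is binary.

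**Conclusion.** The point holds as an error in the stated basis for the client sample. The printed formula with the printed client inputs gives 26, not 1600, and no variance possible on a percentage scale closes the gap at a 10-point difference. The legend is internally inconsistent and belongs to neither calculation. These conclusions need only the document's own figures, and nothing elsewhere in it resolves them.

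The facility calculation is sound on its own inputs (75.3 needed, 80 planned, about 82% power). The cause of the client error is not established. A reader might infer that 1600 is too few, but this has not been shown. Under the binary illustration the stated 80% power would be met at 10 points (about 91%) and missed at 8 (about 75%), so it matters which difference is meant. That illustration is for a single time point at client level. The data analysis section plans a difference-in-difference analysis with the facility as the unit, so the restated power should refer to that analysis.

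**What to change.** Rewrite the paragraph so that each outcome has one set of inputs:

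1. For facility readiness, keep the 10-point difference, variance 400 and design effect 1.2. Say that they give 75.3, rounded up to 80.
2. For client satisfaction, state the measure and its scale, one target difference, one true variance or SD with its source, and one design effect. Use p(1−p) if the measure is binary and the SD of the score if it is continuous.
3. Delete the legend values 59, 19 and 8, or correct them and say which outcome they belong to.
4. Delete the averaging sentence or, if two variances were averaged, say so and give both.
5. If 1600 was set as 80 facilities × 20 clients, say so. Then report the power or detectable difference that 80 facilities and 1600 clients deliver.

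The cost is one paragraph of text and a short recalculation. The numbers of facilities and clients stay as they are. The only possible loss is that the restated power for client satisfaction may be less favourable than 80% if the intended difference is 8 points.

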#### Data collection

We will use trained research assistants to collect data using structured questionnaires on a web-based electronic platform. These questionnaires will be administered in the period preceding and 12 months after the roll-out of autonomy reforms. The health facility questionnaire will be administered to the health facility in charge and other health workers with information on the various sections. It will collect data on the facility profile, target population, services provided, availability of medicine, availability of laboratory services, availability of basic equipment and service utilisation (online supplemental table 1). The health facility assessment questionnaire will evaluate the impact of autonomy on service availability, access to basic equipment, availability of medicines, service utilisation and facility financing (see online supplemental table 1). The client exit interview tool will measure the effects of health facility autonomy on some subjective and objective indicators around service availability and client satisfaction. The exit interviews will seek to establish whether health facility autonomy influences the availability of services and client satisfaction. It will entail questions about the services sought, whether the clients received the services, the client’s perspective on the cost of services, the client’s perspective on facility cleanliness and health worker attitude, how often the clients visit the health facility and whether clients are satisfied with the services (online supplemental table 1).

#### Data analysis

We will compute means, medians and SD of all study variables and key sample characteristics at the baseline and end line. To determine the effects of autonomy reforms on service utilisation and client satisfaction, we will use the quasi-experimental difference-in-difference (DiD) analysis. We will first compute the differences in means between the baseline and end line for each study group, then the differences in mean between the intervention and control.

Thereafter, we will estimate the effect using multivariate regression analysis. This means that we will calculate the DiD while controlling for other covariates that are likely to affect outcomes such as facility average insurance coverage, average distance to facility for facility catchment population, health worker density and facility size. The unit of analysis will be the health facility, and the outcomes of interest will be service utilisation and client satisfaction.

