#### Study population

We intend to assess selected counties, selected facilities and clients receiving services from the selected facilities. For the county assessment, the study population will be the 47 counties from which we have selected 12 counties—4 implementing autonomy reforms, 4 planning to implement and 4 controls. For the facility assessment, the study population will be all county-owned public facilities within the selected counties across all level 2-6 of service provision level 2 (dispensaries), level 3 (health centers) level 4, 5 and 6 (hospitals) (table 1). Level 1 in Kenya comprises community health services, these will be excluded as at the time of the protocol, there were minimal to no mechanisms for payment for services provided at that level. For the client exit interviews, the study population will be all patients or carers whose patients had received services from the selected facilities on the day and time of the survey. These will include patients or carers seeking services such as outpatient services, antenatal services, postnatal services, child welfare services, management of chronic illness and maternity services and those discharged from inpatient care.

**Table 1 T1:** Selected counties with distribution of facilities

Group	County	Level 2	Level 3	Level 4	Level 5	Level 6	Total facilities in county
Controls	Tana River	44	5	3	0	0	52
	Migori	115	19	14	0	0	148
	Embu	88	9	4	1	0	102
	Kirinyaga	47	22	4	0	0	73
Already implementing	Makueni	189	39	12	0	0	240
	Mombasa	40	8	4	1	0	53
	Nakuru	140	26	17	1	0	184
	Kajiado	81	21	5	0	0	107
Intervention	Kakamega	111	48	12	1	0	172
	Lamu	29	3	3	0	0	35
	Homabay	120	48	16	0	0	184
	Nyandarua	54	24	2	0	0	80
	Total by level	1058	272	96	4	0	1430

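### The utilisation difference-in-difference does not protect against the unequal hospital share of the two groups (34 of 80 against 26 of 80), and an additive facility-size covariate would not correct it

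*Protocol article*

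**What the plan says.** The Data analysis section, under the evaluation of effects, sets out two steps for service utilisation and client satisfaction. First, "We will first compute the differences in means between the baseline and end line for each study group", followed by the difference between intervention and control. Then a multivariate regression gives the effect estimate, adjusting for covariates that include facility size. The facility is the unit of analysis. The section mentions no interaction of facility level or size with time, no stratification by level and no scale for utilisation.

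The facility mix is fixed elsewhere. Sample size and sampling says "we will sample all facilities from levels 4–6 from the selected counties", with levels 2 and 3 making up the remainder: "The numbers will be proportionate, targeting a maximum 20 facilities per county". Table 1 ("Selected counties with distribution of facilities") gives the counts by level for each county.

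The Data collection section says that utilisation and the target population are both collected. It refers to an online supplemental table that is not shown.

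**The concern.** A DiD removes fixed differences between groups. It does not remove differences in growth. Dispensaries and hospitals are likely to have very different visit volumes, so the same percentage growth is a much larger absolute rise at a hospital. If one group holds more hospitals, its mean rises more under a trend that everyone shares, and the difference of mean changes counts the excess as an effect of the reform.

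The natural defence is that facility size is among the covariates. Whether it works depends on how size enters the model. A time-invariant covariate entered as a main effect shifts both rounds of a facility equally and has no influence on the DiD coefficient. At stake is a utilisation effect that carries part of the background trend. Utilisation is not the primary outcome (readiness is), but it is one of the two outcomes that the Data analysis section names for the DiD.

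**Working it through.** **The plan's own figure.** The article says "we will randomly sample 80 health facilities per group, assuming a mean difference of 10% in facility readiness between the two groups", with "a population variance of 400 across the groups using 80% power, 95% confidence level and a design effect of 1.2". That gives 2 × 400 × (1.96 + 0.84)² / 10² × 1.2 = 75.3, so 76. The stated 80 is 4 counties × 20, a rounding up. It is sized on readiness. The article gives no sample size for utilisation.

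**Step 1: level 4–6 facilities per group (Table 1).**
- Control: Tana River 3, Migori 14, Embu 4 + 1 = 5, Kirinyaga 4. Total 26 of 80 (32.5%).
- Intervention: Kakamega 12 + 1 = 13, Lamu 3, Homabay 16, Nyandarua 2. Total 34 of 80 (42.5%).

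**Step 2: expected full mix.** Each county's remaining places (20 minus its level 4–6 count) are split in proportion to its level 2 and level 3 counts.

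| Group | Level 2 | Level 3 | Level 4–6 |
|---|---|---|---|
| Control | 44.9 | 9.1 | 26 |
| Intervention | 35.6 | 10.4 | 34 |

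**Step 3: the leak.** Suppose that every facility grows by the same proportion g and the reform does nothing. Then

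DiD = g × (intervention baseline mean − control baseline mean),

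and as a share of the control group's own growth this is (intervention mean − control mean) / control mean, whatever g is.

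The article gives no visit volumes, so those below are assumptions: 400 a month at level 2, 1000 at level 3, and three values for hospitals.

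| Hospital volume (ratio to level 2) | Control mean | Intervention mean | False DiD at g = 10% | Share of shared trend |
|---|---|---|---|---|
| 3000 (7.5) | 1313 | 1583 | +27 | 21% |
| 5000 (12.5) | 1963 | 2433 | +47 | 24% |
| 10,000 (25) | 3588 | 4558 | +97 | 27% |

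At a ratio of 5, with level 3 equal to level 2, the relative means are 2.30 and 2.70, so the share is 0.40 / 2.30 = 17%. With 17% to 24% leaking, 10% growth produces a false effect of about 1.7% to 2.4% of the control baseline. At a ratio of 25 it is 2.7%.

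**Step 4: does the covariate help?** Ordinary least squares was fitted to two rounds with no reform effect and 10% growth everywhere, using volumes of 500, 1000 and 5000 and the mix rounded to whole facilities (45/9/26 and 36/10/34). The baseline means are 2018.75 and 2475, so the expected leak is 0.10 × 456.25 = 45.6.

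| Model | DiD (visits per facility) |
|---|---|
| No covariate | +45.6 |
| Facility size, additive | +45.6 |
| Facility level, additive | +45.6 |
| Size × time | 0 |
| Level × time | 0 |
| Log visits, no covariate | 0 |

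**Step 5: size against noise.** A simulation of 2000 trials used the Step 4 volumes, a log-SD of 0.6 between facilities within a level, a log-SD of 0.15 in change and no county clustering (all assumed). The mean bias was about +50 visits against a standard error of about 103, and the test rejected in 6.6% of trials at a nominal 5%. Regressing the change on baseline volume brought the bias to about −1 visit.

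**The case against.** The strongest reply is that the article does not commit to the analysis that would be biased. It says neither raw nor linear. Multivariate regression could include a log-link count model, the indicator definitions are in a supplement that is not shown, and target population is collected, so a rate may be intended. The differences in means are only the first step. Facility size is named, and if it enters by interaction with time, or if change is regressed on baseline size, the bias goes. All of this stands. A reader might infer that the plan prescribes a raw-count linear analysis and is therefore biased, but the text does not support that.

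The magnitude also has limits. The volumes and growth rates are assumed, most of a shared trend still cancels, and equal absolute growth at every level gives no bias. Parallel trends are an assumption on some scale whichever scale is chosen.

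A reader might also infer that the weight of hospitals in the average conflicts with a study of primary healthcare. It does not. The Background treats first referral hospitals as part of that care, the study population covers levels 2 to 6, and the sampling section gives a reason for taking every level 4–6 facility.

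What the reply does not remove is that the imbalance follows from the plan's own rule and table, and that the two steps as written do not deal with growth that differs by level.

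**Conclusion.** The point holds as a conditional weakness with an inexpensive remedy. The 34 against 26 split rests only on Table 1 and the sampling rule, with all level 4–6 facilities taking part and the cap of 20 reached in each county. It is exact algebra that an additive, fixed facility-size covariate leaves the two-round DiD unchanged. The size of the harm depends on three assumptions: that utilisation is analysed as visit counts, that growth is roughly proportional to volume, and that hospital-to-dispensary volume ratios lie between 5 and 25. Then 17% to 27% of a shared trend appears as a reform effect. At 10% growth that is about half a standard error under the assumed noise, and false positives rise from 5% to between 6% and 7%. County clustering, left out of the simulation, would make the bias smaller still relative to sampling error. This does not threaten the study, and it does not concern the primary outcome.

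**What to change.** In the Data analysis section, estimate the utilisation DiD with facility fixed effects and level-by-round terms for three classes (level 2, level 3, level 4–6). Alternatively, estimate it within each class and combine the results with one set of weights for both groups. Name the main scale: log visits, a count model with a log link, or a rate per target population. Keep the level-by-round terms whichever scale is used, because percentage growth or the rate may itself differ by level. Keep the unadjusted differences in means as description.

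This needs no new data. Three classes add two interaction parameters, so a few degrees of freedom are lost. On the log scales the effect is reported as a percentage change and not as a number of visits, and facilities that report zero visits need the count model. If the supplement or a separate analysis plan already fixes the scale and the level-by-round terms, a cross-reference in this section is enough.

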### Evaluation framework: theory of change (ToC)

This study will be guided by a ToC (figure 1) which we developed from reviewing literature on the relationship between facility autonomy and facility performance and a co-creation workshop that brought together 25 health sector stakeholders drawn from the national and county level and government and development partners. The ToC assumes that facility autonomy spans key functions of the facility including strategic management, financial, procurement, human resource management and facility administration.^7^ This autonomy will require effective legislation, a favourable political environment, facility managerial capacity, facility capacity to claim reimbursements, facility governance structures, increased facility decision space, complementary funding from counties, roll-out of financial management information system to facility level and established accountability mechanisms.^4^ The key activities will include training to management, specification of actor roles, functional facility boards and committees, functional health management committees, setting measurable targets, delegation of authority to the facility management teams, establishment of facilities as procurement entities, county oversight - approval of Authority to Incur Expenditure, supportive supervision by the county and sub-CHMTs, integration of facility and county planning, subsidisation of the cost of care for the poor to guard against inequity, generation of performance data and mobilisation of funds.^47 21^,^23^

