**Figure 1 F1:**
[figure not shown]
Theory of change. PHC, primary healthcare.

The immediate outputs expected from the inputs and activities include timely decision-making, enhanced community participation in facility,^7 24 25^ effective management of staff,^24 25^ reduced bureaucracies in procurement and recruitment, increased community awareness of services implementation of planned activities,^7 26^ increased access and use of facility funds,^7 26^ enhanced predictability on financing,^4^ timely payment of salaries,^4 26^ timely procurement^4 26^ and, finally, effective planning for services.

The expected medium-term outcomes include increased budget responsiveness to needs, enhanced resource mobilisation, increased retention of managers, improved staffing, increased staff motivation,^7 26 27^ reduced absenteeism, increased Human Resources for Health (HRH) productivity,^4 24 25^ improved availability of basic services, reduced stockout of essential medicines, cost consciousness, improved reporting, improved citizen accountability and participation, improved facility management and ordering of medicines and supplies based on need. These medium-term goals should then result in the achievement of the following long-term goals: improved access to services, improved quality of services, enhanced facility efficiency, improved sustainable PHC financing, improved accountability, increased client satisfaction, increased service demand/utilisation and efficient referrals.^4 7 26 27^

From the literature, the effect of autonomy reforms is subject to context which is determined by institutional, socioeconomic and geographic factors.^12^ As such, we will monitor constraints that are likely to influence the effectiveness of the reform including weak legislation, dysfunctional boards/committees, limited decision space, political pressures, cash disbursement delays and poor preparation/training.^4 8^

Finally, autonomy reforms may have unintended negative consequences including increased cost of services, misappropriation of funds, ignoring basic services that do not generate revenue, over-reliance on user fees, reshaping quality based on ability to pay, lower quality of goods and services, increased facility debts and increased out of pocket payments. We will monitor the possible unintended consequences and document the efforts by counties to mitigate them.

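### The adjusted difference-in-difference controls for health worker density, which the theory of change names as a result of the reform, without restricting it to pre-reform values

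*Protocol article*

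**What the plan says.** The Data analysis section of the quantitative component plans two steps. The first is a raw comparison: "We will first compute the differences in means between the baseline and end line for each study group", then the contrast of intervention with control. The second is a regression, and this is the step described as estimating the effect: "we will calculate the DiD while controlling for other covariates that are likely to affect outcomes such as facility average insurance coverage", continuing with "average distance to facility for facility catchment population, health worker density and facility size". The unit of analysis is the facility, and the outcomes are service utilisation and client satisfaction. The time at which the covariates are measured is not given. The Data collection section has questionnaires before roll-out and again 12 months after it, so values could come from either wave.

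The theory of change, in the text following Figure 1, lists among the immediate outputs of autonomy "reduced bureaucracies in procurement and recruitment" and among the medium-term outcomes "increased retention of managers, improved staffing, increased staff motivation". It then says "These medium-term goals should then result in the achievement of the following long-term goals", and those goals include "increased client satisfaction, increased service demand/utilisation and efficient referrals".

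**The concern.** The protocol's causal account runs from autonomy to staffing, and from staffing to satisfaction and utilisation. The regression meant to measure the effect of autonomy on those two outcomes holds staffing density constant. Covariates are chosen because they probably affect outcomes, a criterion that admits variables on the causal path as readily as confounders. The list is also open-ended.

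What is at stake is the meaning of the adjusted estimate. The study sets out to measure what autonomy does to facility performance, including anything it achieves through better staffing. A model that conditions on post-reform staffing answers a narrower question, namely the effect not transmitted through staffing. That would understate the reform if staffing is one of the ways it works. Methodological rigour also commits the study to aligning its analysis with the theory of change, and this covariate does not fit that commitment.

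**Working it through.** The protocol states no figure on this point to reproduce. The check compares the covariates with the theory of change and then works through the possible specifications.

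**1. Each covariate against the theory of change**

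| Covariate | Named as a reform output, outcome or goal? |
|---|---|
| Health worker density | Yes: improved staffing is a medium-term outcome that leads to the analysed outcomes |
| Insurance coverage | No. The nearest text is "facility capacity to claim reimbursements", which is a requirement for autonomy |
| Facility size | No |
| Distance to facility | No |

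The conflict in the text therefore concerns health worker density alone.

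**2. Staffing as measured at each wave enters the model**

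Let the total effect be 10 units (a scale only) and let a share m run through staffing. Conditioning on current staffing leaves the direct part, 10 × (1 − m):

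- m = 10%: 10 × 0.90 = 9.0
- m = 25%: 10 × 0.75 = 7.5
- m = 50%: 10 × 0.50 = 5.0

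A simulation agrees. It used 80 facilities per arm, two waves, ordinary least squares with group, time and group × time, and 1000 runs. The other settings were assumed: 4 outcome units per unit of staffing, a baseline staffing difference of 0.3 between arms, facility SD 15 and residual SD 10.

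| Assumed share | Unadjusted | Wave-specific staffing | Baseline staffing, main effect |
|---|---|---|---|
| 0% | 10.04 | 10.03 | 10.04 |
| 10% | 10.06 | 9.07 | 10.06 |
| 25% | 9.93 | 7.45 | 9.93 |
| 50% | 9.92 | 4.94 | 9.92 |

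**3. Baseline values enter as main effects only**

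In a balanced two-wave panel, the group × time term residualised on group and time equals (g − ḡ)(t − ½). Within one facility this sums over t = 0 and t = 1 to (g − ḡ)(−½ + ½) = 0. It is therefore orthogonal to any covariate that is constant within a facility, and the DiD coefficient is exactly unchanged. That is why the second and fourth columns of the table match. No bias is introduced, but trend differences are not adjusted for either. These matter because Sample size and sampling says the counties are chosen purposively.

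**4. Baseline values enter with a time interaction**

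With two waves, facility fixed effects plus baseline covariate × end-line terms is the same model as regressing each facility's change on group and baseline covariates. Post-reform staffing stays out, and trends are allowed to differ by baseline characteristics.

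**The case against.** **Timing is commonly left to a fuller document.** Which wave's covariate values are used could well be settled in a full protocol or analysis plan that is not shown. Silence on timing alone would not be a finding. However, the article itself names health worker density as a control in the effect model and improved staffing as an effect of the reform, and that conflict is in the text.

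**The text can be read as a sound model.** It describes differences from baseline to end line and then a facility-level regression, which is compatible with regressing change on baseline covariates. This stands: a reader might infer that the stated adjustment fails however it is read, and that is not so. The wording permits this reading but does not select it.

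**Only staffing is affected.** A reader might extend the point to insurance coverage and facility size. The documents do not list either as something the reform should change. An effect on them is conceivable, but that is inference.

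**The total effect is estimated anyway.** The raw DiD contains no mediator and would show any attenuation beside it. This limits the harm. Still, the regression is the step described as estimating the effect.

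**Staffing may change for other reasons.** Counties may hire or lose staff independently of the reform, and the new law is described as giving some financial and procurement autonomy, so the staffing route within 12 months is uncertain. Both points are fair. They support a labelled sensitivity analysis, but not post-reform staffing in the main model.

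**No power loss can be read off.** A reader might put the readiness inputs (variance 400, design effect 1.2, 80 per group) into SE = √(2 × 400 × 1.2 / 80) = 3.46 and see power fall from 82% at 10 units to 52% at 7 or 30% at 5. The arithmetic is right, but those inputs describe a single-wave comparison of readiness, not a DiD on utilisation or satisfaction, and the reduced effects rest on assumed shares.

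**Conclusion.** The point holds for health worker density. The protocol's effect model controls for a variable that its own theory of change places between the reform and the analysed outcomes, and nothing confines that variable to pre-reform values.

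The bias is conditional. It arises only if post-reform staffing enters the model and staffing carries part of the effect. It is then about equal to the mediated share: a tenth, a quarter or a half of the effect at assumed shares of 10%, 25% and 50%. The documents do not support any particular share, so it cannot be said that the planned estimate is in fact attenuated. Baseline main effects in a balanced panel would cause no such bias but would adjust nothing. A change-score regression on baseline covariates would be sound. The plan should say which is meant, because the three answer different questions or adjust for different things.

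**What to change.** Add to Data analysis:

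- The main model adjusts only for the pre-reform value of health worker density, interacted with the end-line indicator. Equivalently, facility-level change is regressed on group and baseline covariates.
- Insurance coverage, distance and facility size are also taken at baseline and handled in the same way, as a precaution.
- Post-reform staffing does not enter the main effect model. Any model containing it is labelled a mediation or sensitivity analysis.
- The unadjusted DiD continues to be reported beside the adjusted one.

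The cost is one or two sentences and a few more model terms. These terms address only those trend differences that relate to the chosen baseline variables. The one practical condition is that baseline values exist. The questionnaire content in Data collection does not name health worker density, insurance coverage or distance, and the supplementary table it cites is not available here, so this needs confirming. A covariate without a baseline value should be left out of the main model rather than replaced by its end-line value.
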